# Study protocol for a controlled trial of an eHealth system utilising patient reported outcome measures for personalised treatment and care: PROMPT-Care 2.0

**DOI:** 10.1186/s12885-018-4729-3

**Published:** 2018-08-23

**Keywords:** Patient-reported outcomes (PROs), eHealth, Patient-centred care, Electronic health record, Self-management, Risk-stratified care, Screening, Non-randomized control trial, Supportive care, Survivorship care

## Abstract

**Background:**

Routine assessment and clinical utilisation of patient-reported outcome (PRO) measures can lead to improved patient outcomes. The PROMPT-Care eHealth system facilitates PRO data capture from cancer patients, data linkage and retrieval to support clinical decisions, patient self-management, and shared care. Pilot testing demonstrated acceptability and feasibility of PROMPT-Care Version 1.0. This study aims to implement PROMPT-Care Version 2.0 and determine its efficacy in reducing emergency department (ED) presentations, and improving chemotherapy delivery and health service referrals, compared to usual care.

**Methods:**

Groups eligible to participate in the intervention arm of this controlled trial are patients receiving cancer care (including follow-up). PROMPT-Care patients will complete monthly assessments (distress, symptoms, unmet needs) until voluntary withdrawal or death. In Version 1.0, the care team accessed patients’ clinical feedback reports in ‘real time’ to guide their care, and patients received links to support their self-management, tailored to their PRO responses. Version 2.0 was extended to include: i) an additional alert system notifying the care team of ongoing unresolved clinical issues, ii) patient self-management resources, and iii) an auto-populated Treatment Summary and Survivorship Care Plan (SCP). The control population will be patients extracted from hospital databases of the general cancer patient population who were seen at the participating cancer therapy centres during the study period, with a ratio of 1:4 of intervention to control patients.

A minimum sample size of 1760 (352 intervention and 1408 control) patients will detect a 14% reduction in the number of ED presentations (primary outcome) in the PROMPT-Care group compared with the control group. Intervention patients will provide feedback on system usability and value of the self-management materials; oncology staff will provide feedback on usefulness of PROMPT-Care reports, response to clinical alerts, impact on routine care, and usefulness of the SCPs; and GPs will provide feedback on the usefulness of the SCPs and attitudes towards shared-care models of survivorship care planning.

**Discussion:**

This study will inform the PROMPT-Care system’s impact on healthcare utilisation and utility as an alternative model for ongoing supportive care.

**Trial registration:**

Australian New Zealand Clinical Trials Registry (ACTRN12616000615482) on 12th May 2016 (www.anzctr.org.au).

## Background

Patient-reported outcomes (PROs) clearly place the patient’s voice at the forefront of health care delivery [1], with systems to routinely collect and utilise PROs in clinical settings demonstrated to be feasible and acceptable [2–5]. Routinely screening for symptoms and other PROs and utilising these data to inform patient care has also been demonstrated to lead to significant improvements in patient outcomes and care indicators. In particular, reductions in emergency department visits [6, 7], longer tolerability of chemotherapy [6], improvements in both short- and long-term survival [6, 8], improved health related quality of life [9] and improved communication between patients and clinicians [9–11] have been documented in oncology settings. PROs have also been effectively used in non-oncology settings, including to inform surgical decisions in the orthopaedic setting [12, 13].

We have previously reported the development and acceptability and feasibility testing of an integrated PRO eHealth system, PROMPT-Care (**P**atient **R**eported **O**utcome **M**easures for **P**ersonalised **T**reatment and **Care**) [14, 15]. This system supports routine collection and analysis of cancer patients’ PROs, real-time feedback of PRO results to their cancer care team to inform patient-centred care, and delivers evidence based self-management information to address patient reported problems. Our feasibility study demonstrated that the PROMPT-Care eHealth system is acceptable to the users, i.e. to the patients and cancer care team, and potentially feasible to implement in cancer centres [15]. Integration of the PRO measures into the hospital’s point-of-care oncology information system (OIS), a key feature distinguishing PROMPT-Care from previous oncology-based eHealth systems, was hypothesised to enhance their relevance and usefulness in informing routine cancer care [16]. Our previous testing was not designed to inform the utility elements of the PROMPT-Care system or its efficacy. Therefore, this will be the primary purpose of the proposed study.

We have used the term *patient* in reference to all people diagnosed with cancer who are currently on treatment and in follow-up.

### Objective

The overall objective of this study is to implement the PROMPT-Care 2.0 eHealth platform and determine its efficacy among cancer patients at four tertiary hospitals. Specifically, this study will test whether web-based routine collection of PROs, combined with automated alerts to clinical teams and provision of patient self-management resources, result in reduced emergency department presentations, and improved chemotherapy delivery and health service referrals. The study will also evaluate system utility and potential benefits and barriers to PROMPT-Care implementation in routine care from both the patient and healthcare professional perspective.

## Methods/design

### Setting

The study is being undertaken in the cancer therapy centres of four participating hospitals, with oversight of the implementation undertaken by a clinical study lead: Liverpool Cancer Therapy Centre and Macarthur Cancer Therapy Centre (GD), Illawarra Cancer Care Centre and Shoalhaven Cancer Care Centre (AA).

### Ethics approval

Ethics approval was obtained from the Human Research Ethics Committees of South Western Sydney, and Illawarra Shoalhaven Local Health Districts (Reference No. HREC/15/LPOOL/287).

### PROMPT-care intervention

As previously reported [14, 15], the PROMPT-Care platform facilitates patients completing PRO measures online through standardised assessment tools using an electronic device (e.g. tablet, iPad, smart phone, or computer) and automatically converts these data into a format (HL7 messages) [17] that is transferred directly into the patient’s point-of-care OIS in ‘real time’, following an automated matching verification process to ensure the correct record is populated. The point of care system used in this trial was Mosaiq ™ (Elekta Medical Systems, Sunnyvale, CA). PROs assessed include: Distress Thermometer (DT) and associated checklist [18], the Edmonton Symptom Assessment Scale (ESAS) [19], and the Supportive Care Needs Survey-Screening Tool 9 (SCNS-ST9) [20].

Feedback received during feasibility testing of pilot configuration for the PROMPT-Care system (Version 1.0) [15], highlighted additional patient and clinical team needs. As a result, Version 2.0 of the PROMPT-Care system has been extended to include the following elements: i) an additional alert system notifying the cancer care team of patients with ongoing unresolved issues, ii) tiered patient self-management resources, and iii) an auto-populated Treatment Summary and Survivorship Care Plan (SCP).

Version 2.0 of the PROMPT-Care intervention consists of three components (Fig. 1.):

**Fig. 1 Fig1:**
[figure not shown]
PROMPT-Care 2.0 system overview

Timely clinical careClinical feedback reportsUsing previously reported algorithms [21], the uploaded PRO data is presented in a clinical feedback report (Fig. 2), which includes a basic one-page summary of the results of the most recent assessment, recommended clinical actions and suggested referrals, as well as a longitudinal report (Fig. 3) of patients’ scores over time on the PRO scales. The reports are available ‘real time’ for clinical staff to review in the clinic with patients.

**Fig. 2 Fig2:**
[figure not shown]
Sample clinical feedback report

**Fig. 3 Fig3:**
[figure not shown]
Sample longitudinal feedback reportClinical alertsIf the patient’s scores on any of the PROs breach a predefined threshold on two consecutive assessments, an automated alert will be generated in the OIS, with an email received by a designated member of the cancer centre team, who will review the PROMPT-Care report and follow the care pathway agreed for that cancer centre.Tiered patient self-management

Upon completing their PROMPT-Care assessment, patients will receive an email which directs them to a website containing tailored self-management information resources (Fig. 4) to address issues of concern they identified in their assessment. In response to patient feedback in the feasibility study [15], the PROMPT-Care system was modified to provide patients with a tiered approach to their self-management support. The first time a patient breaches a PRO item, they will receive a link to generic information resources via one of the four distinct domain-specific webpages hosted on the Cancer Institute NSW eviQ website: emotional well-being, physical well-being, social/family well-being, practical problems. Patients who do not breach any items will receive a link to the “maintaining well-being” page, to support their continued general health. If a patient breaches the same item on two consecutive PROMPT-Care assessments, they will receive a link to more dynamic and interactive resources such as videos, podcasts, or interactive self-help programs (where available), as well as links to resources to facilitate effective communication with their GP and appointment preparation.3.Shared follow up care

**Fig. 4 Fig4:**
[figure not shown]
Screenshot of patient self-management Tier I and Tier II pages (emotional well-being)

For patients who complete their primary treatment (chemotherapy, radiotherapy) and transition to follow-up care during the trial, an auto-populated Treatment Summary will be generated within the OIS, approved by the treating clinicians, and then sent to both the patient and their nominated GP. The treatment summary will contain information regarding the patient’s diagnosis, treatments received, complications, ongoing medications, and support services to which the patient was referred. For patients diagnosed with colorectal, prostate, breast or gynaecological cancers, an accompanying SCP, summarising potential long-term effects of treatment, recommended tests and follow-up appointments will also be sent.

### Study population

#### Patients

Eligible patients are people who are either currently receiving cancer care (including follow-up care) or have recently been diagnosed with cancer and are scheduled to commence cancer treatment at one of the four participating sites. Eligibility criteria include a confirmed diagnosis of cancer, age 18 years or over, cognitively able to provide informed consent and understand the surveys, and ability to complete the survey in English. Exclusion criteria are having a diagnosis of a blood cancer and not having access to the Internet outside of the clinic.

#### Oncology staff

All staff who provide care in the oncology departments at the participating hospitals are eligible to participate.

#### General practitioners (GPs)

All GPs nominated by a participating patient as their primary care provider will be eligible to participate.

### Control population

A list of potential control individuals (minimum *n* = 1408) will be extracted from hospital databases of the general cancer patient population who were seen at the participating cancer therapy centres during the study period.

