#### Patient identification and consent

Participating clinicians will review their clinic lists to identify eligible patients who have appointments scheduled within the coming two (2) months. Two patient recruitment approaches will be utilised to achieve a similar proportion of both patients in active treatment and those in follow-up care.

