#### Patient clinical and socio-demographic characteristics

Upon consenting, participants will complete a questionnaire about socio-demographics including: marital status, education level, employment status and language spoken at home. Additional demographics (eg. age, gender and need for interpreter) and clinical characteristics such as date of diagnosis, site (ICD-10), stage (TNM classification) and treatment details will be extracted from the OIS.

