### Statistical analyses

Descriptive statistics will be generated for all socio-demographic and clinical characteristics, and outcome measures. A multivariable Poisson or negative binomial regression (depending on over-dispersion) will be used to determine whether the rates of ED presentations were different between the PROMPT-Care and control groups adjusting for covariates (such as age, sex, stage of disease, and treatment status). Number of referrals to allied health services will be analysed similarly. Multivariable Cox proportional hazards model will be used to analyse length of time from start to end of chemotherapy adjusting for covariates.

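### The control group is defined without the eligibility rules that bind intervention patients, so blood-cancer and non-English-speaking patients can enter the control arm only and may bias the primary ED rate ratio

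*Protocol article*

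**What the plan says.** All references are to the protocol article.

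- **Intervention patients** (Study population, Patients): they need a confirmed cancer diagnosis and must be at least 18. A further requirement is being "cognitively able to provide informed consent and understand the surveys, and ability to complete the survey in English". The section adds: "Exclusion criteria are having a diagnosis of a blood cancer and not having access to the Internet outside of the clinic".
- **Where eligibility applies** (Abstract, Methods): the rule is tied to one arm, "Groups eligible to participate in the intervention arm of this controlled trial are patients receiving cancer care (including follow-up".
- **Controls** (Control population): "A list of potential control individuals", at least 1408 of them, is to be "extracted from hospital databases of the general cancer patient population who were seen at the participating cancer therapy centres during the study period". The abstract gives the same source and omits the word *potential*. No section applies the patient criteria to controls or describes a later screen, restriction or matching.
- **Analysis** (Statistical analyses): Poisson or negative binomial regression of ED presentations, "adjusting for covariates (such as age, sex, stage of disease, and treatment status").
- **Available data** (Patient clinical and socio-demographic characteristics): the fields taken from the oncology information system include "Additional demographics (eg. age, gender and need for interpreter) and clinical characteristics such as date of diagnosis, site (ICD-10), stage (TNM classification").

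**The concern.** The trial is not randomised, so the definition of the control group carries most of the weight of the comparison. If a kind of patient is barred from one arm and admitted to the other, the rate ratio compares two different populations.

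Adjustment works by comparing like with like inside each covariate level. Where a level has controls but no intervention patients, there is nothing to compare. At best, a blood-cancer term in the model would remove those controls from the contrast, which is restriction by another route, and no such term is named. Age, sex, stage and treatment status do not stand in for tumour type, language, cognition or Internet access.

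At stake is the primary outcome. A difference in ED use that comes only from who was admitted to the control arm could be read as an effect of PROMPT-Care, or could hide one.

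**Working it through.** **1. The plan's own figure.** Inputs from Sample size: control rate 1.4 visits per patient, 14% reduction (rate ratio 0.86, intervention rate 1.4 × 0.86 = 1.204), ratio 1:4, 80% power, 5% significance (taken as two-sided). With a Wald test on the log rate ratio and Poisson variance:

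n(intervention) = (1.960 + 0.842)² × [1/1.204 + 1/(4 × 1.4)] / (ln 0.86)² = 348.2, so 349, with 4 × 349 = 1396 controls and 1745 in total.

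The plan states 352, 1408 and 1760, which agrees within 3%. Power at 352/1408 is 80.4%. The sample size is sound; the point concerns comparability only.

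**2. The two definitions side by side.**

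| Criterion | Intervention | Control | Checkable from named fields? |
|---|---|---|---|
| Age 18 or over | required | not stated | yes (age) |
| No blood cancer | required | not stated | yes (ICD-10 site) |
| Survey in English | required | not stated | in part (need for interpreter) |
| Cognitively able | required | not stated | no field named |
| Internet outside clinic | required | not stated | no field named |

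**3. Possible size of the bias.** The documents give no ED rate and no share for any excluded group, so both are assumptions here. Let p be the share of controls who would fail the intervention criteria and r their ED rate relative to other controls. Assume no true effect, and that the named covariates absorb none of the difference. Then

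apparent rate ratio = 1 / [1 + p(r − 1)].

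The chance of a falsely significant benefit at 352/1408, with m = 1 + p(r − 1), is Φ(ln m / SE − 1.960), where SE = √[1/(352 × 1.4) + 1/(1408 × 1.4m)].

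| p | r | Apparent rate ratio | Spurious reduction | Chance of false significance |
|---|---|---|---|---|
| 5% | 2 | 1/1.05 = 0.95 | 4.8% | 16% |
| 10% | 2 | 1/1.10 = 0.91 | 9.1% | 48% |
| 15% | 2 | 1/1.15 = 0.87 | 13.0% | 80% |
| 10% | 3 | 1/1.20 = 0.83 | 16.7% | 96% |

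The chances use Poisson variance. Over-dispersion would lower them but would leave the bias itself unchanged.

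**4. When the whole target effect appears.** Setting the ratio to 0.86 gives p = (1/0.86 − 1)/(r − 1) = 0.163/(r − 1): 33% at r = 1.5, 16% at r = 2, 8% at r = 3.

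**5. The other direction.** If the excluded patients attend ED half as often (r = 0.5) and form 10% of controls, the ratio is 1/0.95 = 1.05, which works against the intervention.

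**The case against.** The strongest reply is that silence is being read as a rule. The article condenses a fuller protocol, and its control section speaks of *potential* individuals, which suggests a source pool to be filtered later. Nothing says that blood-cancer patients will be controls. It stands that their inclusion is permitted rather than confirmed; a reader who infers that they will certainly be there goes beyond the text. The reply does not clear the plan, however. No later screen is described, the abstract omits the qualifying word, and the minimum list size of 1408 equals the number of controls required, so a list of that size leaves no room for removals. Who the controls are is also a design decision that the article fixes twice, in terms that differ from the patient criteria.

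The covariate list is open-ended and ICD-10 site is among the extracted data, so tumour type may yet be added. That would help for solid tumours present in both arms, but would give no comparison for a stratum confined to controls.

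Two further inferences are tempting and are not supported:

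- Recruitment aims to "achieve a similar proportion of both patients in active treatment and those in follow-up care", whereas controls keep whatever mix occurs. Treatment status is a named covariate and nothing confines either status to one arm, so the planned model can address this.
- Read literally, the control source includes PROMPT-Care participants. The article describes two separate groups, so this reading is strained, and any overlap would pull the ratio towards 1.

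**Conclusion.** The point holds in this form: the article applies its eligibility rules to intervention patients only, and its control definition permits strata that the intervention arm cannot contain and that the planned regression cannot balance. The primary rate ratio could therefore be biased.

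Size and direction are not established. At twice the ED rate, shares of 5% to 15% give spurious reductions of 4.8% to 13.0%, just short of the 14% target, which needs about 16%. These figures rest on assumed shares and rates, no true effect, and no help from the named covariates. A reader might conclude that the bias must favour PROMPT-Care. The documents give no subgroup ED rates, so that does not follow; with lower attendance among the excluded patients it reverses.

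**What to change.** In the Control population section, state that controls must meet every patient criterion that hospital data can verify: at least age 18 or over and no blood-cancer ICD-10 code, with no recorded need for an interpreter as a proxy for English ability. State also that PROMPT-Care participants are not eligible as controls, and that the minimum of 1408 applies after these filters.

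In Statistical analyses, add tumour site to the named covariates, or match on it. Stratified sampling of controls is one way to do this, not a necessity.

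State as a limitation that Internet access, and cognition where it is not recorded, cannot be checked in controls.

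The cost is a few query filters and a smaller control pool. For example, if 10% were removed (an assumption), 1408/0.9 = 1564.4, so 1565 records would have to be extracted to keep 1408. Age, ICD-10 site and interpreter need are fields that the article already names, although it describes them for participants, so their availability for controls should be confirmed. No input to the 352/1408 calculation changes.

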##### Mail-out

For patients who require additional time to consider participation, or those in follow-up who do not have regular clinic appointments, research staff will mail out a study pack inviting them to participate, then follow up by phone to answer any questions and provide additional information, as required.

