#### Assessment completion

Patients will complete PROMPT-Care assessments on a monthly basis and will be followed up for a minimum of four months. Patients will have the option to complete assessments either at the hospital in clinic, their home or any public community location. Patients completing assessments in clinic will be provided with a tablet device in the waiting area just prior to their scheduled appointment. Patients who complete assessments from home or in community locations will receive an email containing the survey link three days before their assessment is due.

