### Measures

#### Outcomes

The primary outcome is number of emergency department (ED) presentations observed during the study period. Details about ED presentation dates, reason for presentation and any resulting admissions will be extracted from the electronic medical record (EMR) (Table 1).

**Table 1 Tab1:** Primary and secondary outcome data collected

Data	Description of data	Source of data
Primary Outcomes		
Emergency Department (ED) presentations	• ED presentations (date, number of visits) • Length of stay • Reason for presentation	Extracted from electronic medical record (EMR)
Secondary Outcomes		
Time on chemotherapy	• Planned chemotherapy regimen • Actual regimen start and end date • Toxicities, changes to treatment delivery and reasons	Extracted from oncology information system (OIS)
Referral to allied health services	• Date of referral and allied health service type • Reason for referral eg. emotional distress, case management etc.	Extracted from EMR & OIS

The secondary outcomes are time receiving active chemotherapy and referrals to allied health services. Details of planned and actual chemotherapy regimens as well as any toxicities and changes to treatment delivery will be extracted from the OIS. Date, reason and number of referrals to allied health services will be tabulated and extracted from the medical record and OIS.

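### Controls qualify by a cancer-centre visit inside the window in which ED presentations are counted, so a visit prompted by an ED presentation can create a control and bias the comparison towards the intervention

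*Protocol article*

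**What the plan says.** Under Control population, a list of potential controls (at least 1408) "will be extracted from hospital databases" covering the "general cancer patient population who were seen at the participating cancer therapy centres during the study period". The Abstract repeats this rule. Under Outcomes: "The primary outcome is number of emergency department (ED) presentations observed during the study period". Control entry and the outcome therefore share one window. The article states no index date for a control and does not require the qualifying visit to be planned.

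Intervention patients enter differently. Under Patient identification and consent: "Participating clinicians will review their clinic lists to identify eligible patients who have appointments scheduled within the coming two (2) months". That section then introduces two recruitment routes, intended "to achieve a similar proportion of both patients in active treatment and those in follow-up care". The Mail-out section covers patients who want more time to decide and also "those in follow-up who do not have regular clinic appointments, research staff will mail out a study pack inviting them to participate". Under Assessment completion, intervention patients "will be followed up for a minimum of four months".

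Under Statistical analyses, the ED comparison is a Poisson or negative binomial regression adjusted for covariates, of which age, sex, stage and treatment status are given as examples.

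**The concern.** An intervention patient is identified through an appointment that exists before follow-up starts. A control is identified afterwards, by any centre visit in the period over which that person's ED presentations are counted. Consider two follow-up patients with no routine visit due in the period. One stays well, is not seen and cannot be a control. The other presents to ED, is reviewed at the cancer centre as a result, and now qualifies. Control membership then depends partly on the outcome.

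If that happens, the control ED rate is too high and an ineffective intervention appears to reduce ED presentations. Both patients are coded as follow-up, so adjusting for treatment status does not separate them. The problem falls on the primary outcome, in a stratum that the trial means to recruit to about half.

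**Working it through.** **1. The plan's own figure.** Sample size section: control rate 1.4, 14% reduction (intervention rate 1.4 × 0.86 = 1.204), ratio 1:4, 80% power, 5% significance (two-sided assumed). Poisson log rate-ratio formula:

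n = (1.960 + 0.842)² × (1/1.204 + 1/(4 × 1.4)) / (ln 0.86)² = 7.849 × 1.0091 / 0.02275 = 348.2.

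That is 349 + 1396 = 1745, against the stated 352 + 1408 = 1760, so the figure is reproduced to within 1%. The present point does not change it.

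**2. Selection within follow-up patients.** Assumed, because the documents give neither: s = chance of a routine centre visit in the period, independent of ED visits; u = chance that any one ED visit leads to a centre visit. ED counts N are Poisson with mean λ. Then P(not seen | N) = (1 − s)(1 − u)^N, and

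- P(seen) = 1 − (1 − s)e^(−λu)
- R = E[N | seen]/λ = [1 − (1 − s)(1 − u)e^(−λu)] / [1 − (1 − s)e^(−λu)]

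For λ = 0.7, s = 0.6, u = 0.3: e^(−0.21) = 0.8106; R = (1 − 0.4 × 0.7 × 0.8106)/(1 − 0.4 × 0.8106) = 0.7730/0.6758 = 1.144, a null rate ratio of 1/1.144 = 0.874. For λ = 1.4 with the same s and u, R = 1.107 and the ratio is 0.903. With u = 0, R = 1 and there is no bias.

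A patient identified through a scheduled visit has mean λ in this model, as does one drawn from the whole follow-up population. The inflation in controls is therefore the same whichever way the mail-out route is read.

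**3. Whole comparison, adjusted for treatment status.** Assume half the intervention arm (176 of 352) is in follow-up and half in active treatment, and active patients are always seen. Controls are drawn from those seen, so 1408/(1 + P) are active and 1408P/(1 + P) are in follow-up, with P = P(seen). The strata are combined with weights w = n₁n₀/(n₁ + n₀):

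RR = (w_a λ_a + w_f λ_f)/(w_a λ_a + w_f λ_f R)

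Example: λ_a = 2.1, λ_f = 0.7 (assumed; they average 1.4), s = 0.6, u = 0.3. Controls 840.2 active and 567.8 follow-up; w_a = 145.5, w_f = 134.4. RR = (305.6 + 94.1)/(305.6 + 94.1 × 1.144) = 399.7/413.2 = 0.967.

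| s | u | RR, rates 2.1 and 0.7 | RR, both rates 1.4 |
|---|---|---|---|
| 0.8 | 0.3 | 0.986 | 0.978 |
| 0.8 | 0.5 | 0.980 | 0.973 |
| 0.6 | 0.3 | 0.967 | 0.951 |
| 0.5 | 0.3 | 0.955 | 0.934 |
| 0.5 | 0.5 | 0.940 | 0.926 |

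The range is about 0.93 to 0.99 with no treatment effect.

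**4. Cross-check by simulation.** One million patients per scenario, mean 1.4, unadjusted, with a fraction f of the whole cohort having no routine visit. The case in step 3 corresponds to f = (1 − s)/2, that is 0.10 to 0.25. For u from 0.1 to 1, the null ratio is 0.96 to 0.99 at f = 10% and 0.89 to 0.97 at f = 25%, covering Poisson counts and negative binomial counts with dispersion 1. The lower ends come from the over-dispersed counts. At f = 5% it is 0.98 to 0.995; at f = 50%, 0.77 to 0.93.

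**5. Consequence for the test.** At a spurious ratio of 0.97 with 352:1408 and control rate 1.4: SE = √(1/(352 × 1.358) + 1/(1408 × 1.4)) = 0.0510, and −ln 0.97 = 0.0305. The chance of a significant ED reduction is Φ(0.0305/0.0510 − 1.960) = 8.7%. With negative binomial dispersion 1 (assumed), SE = √(0.00260 + 1/352 + 1/1408) = 0.0784 and the chance is 5.8%. The nominal value is 2.5%.

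**The case against.** Five points on the other side deserve weight.

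- A reader might infer that an ED presentation by itself makes someone a control. The text does not say so: the criterion is being seen at a cancer therapy centre. The path needs a further step, from ED to a centre visit, which the documents neither describe nor quantify. This stands, and the bias is nil if that step never happens.
- A reader might infer that mail-out recruits need have no appointment at all. Patient identification and consent places both routes after a review of clinic lists for appointments in the next two months, and Mail-out says such patients lack regular appointments, not that they have none. This weakens the contrast between the arms' entry routes but, as step 2 shows, does not remove the inflation in controls.
- A reader might also infer that the intervention rate is biased downward. For example, if 25% of that arm were mail-out patients with half the ED rate, its mean would fall by 12.5%. Both inputs are assumed, and the mechanism is ordinary case mix, not selection on the outcome. The documents do not show it.
- Ratios of 0.87 to 0.90 apply the follow-up visit chance to everyone. About half the intervention arm is meant to be in active treatment, and the model adjusts for treatment status. This stands, and step 3 allows for it.
- The article is condensed and speaks of potential controls, so later selection steps may exist. That excuses missing detail. It does not change the stated rule, and narrowing a list cannot bring back well patients who never entered it.

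**Conclusion.** The point holds as a defect in a stated rule: control entry depends on centre contact inside the outcome window, while intervention entry rests on appointments scheduled beforehand. Followed as written, the rule lets an ED-driven centre visit create a control, and the resulting bias favours the intervention. Under the assumptions in step 3, the adjusted null rate ratio is about 0.93 to 0.99, a spurious reduction of roughly 1% to 7% against a target of 14%. Even 0.97 raises the chance of a false significant reduction from 2.5% to about 6% to 9%. The visit chances, the ED-to-centre step, the stratum rates and the assumption that active patients are always seen are not in the documents. A bias as large as the whole target effect is not supported: in the simulation it needs about half of all patients to have no routine visit.

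**What to change.** Sample controls from the participating centres' scheduled appointment lists, as is done for intervention patients, and start counting their ED presentations from that scheduled visit. Exclude entry through an attendance that results from an ED presentation or admission. Repeat the primary comparison without mail-out recruits as a sensitivity analysis. Settle the rule before the control data are extracted.

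The cost is a revised extraction query on hospital systems already in use, a short change to the protocol text, and a smaller pool of candidate controls, which should be checked against the required 1408.
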